## Abstract

**Background:**

Internet-based self-help interventions (IBIs) have proven effective in reducing depression, especially in high and middle-income countries, and have proven to be flexible and location-independent. However, unguided IBIs often face high dropout rates, low uptake, lower adherence, and reduced effectiveness.

**Objective:**

This study evaluates the effectiveness of a self-help program against depressive symptoms (Deprexis) with or without peer-to-peer support, focusing on cultural differences between WEIRD (Western, Educated, Industrialized, Rich, and Democratic) and non-WEIRD countries, specifically Switzerland and India. Additionally, this research explores Deprexis’s efficacy in French-speaking Switzerland, aiming to extend its benefits to this demographic. The study also investigates mood responses to monetary and social rewards using the Fribourg Reward Task to understand the relationship between depression and reward system dysfunction in a cross-cultural context.

**Methods:**

The study is a randomized controlled trial; participants with mild to moderate depression will be randomized into three groups of 80 each: Deprexis only, Deprexis with peer-to-peer support, and a control group on a waiting list. The intervention lasts 8 weeks, with measurements at baseline (T0), mid-intervention (4 weeks, T1), post-intervention (8 weeks, T2), and follow-up (3 months post-intervention, T3). Participants will complete online questionnaires on RedCap and the Fribourg Reward Task. Primary outcome: depressive symptoms at 8 weeks post-intervention. Secondary outcomes: mood responses to reward, pleasure, and social support, with moderators and mediators like anxiety, stress, quality of life, PTSD, childhood trauma, self-efficacy, and self-esteem.

**Results:**

The study, registered at ClinicalTrials.gov (NCT06480474) and Swiss National Clinical Trials (SNCTP000005917), was approved by the Ethics Committee of Vaud (CER-VD) in May 2024 (protocol date: 22.05.2024; version: 4; 2023-D0112). Recruitment began in June 2024 and is expected to end in May 2026.

**Conclusion:**

This study examines the potential of IBIs, including peer-to-peer support forums and the Deprexis program, in addressing depression globally. It investigates the extent to which cultural adaptations may be required in order to integrate globally available online mental health care into existing health systems to bridge treatment gaps and improve outcomes. Future research should explore these interventions’ effectiveness in diverse cultural settings and their long-term impacts.

**Supplementary Information:**

The online version contains supplementary material available at 10.1186/s13063-025-09377-6.

## Introduction

Before 2020, mental health issues, particularly depression, were already a significant global health burden. The COVID-19 pandemic exacerbated this crisis, with global depression rates rising to 25% in the first year [1]. Depression is often associated with widespread stigma, discrimination, and human rights violations; for instance, lack of proper education, lack of access to information, and inequalities around access to quality mental health services [2–4]. Even before the pandemic, access to effective mental health care was limited, with 71% of individuals with depression worldwide not receiving treatment, showing stark disparities between WEIRD (Western, Educated, Industrialized, Rich, and Democratic) countries (70% treated) and non-WEIRD countries (12% treated) [5]. Despite the availability of effective treatments like psychotherapy, a global treatment gap of 44% persists [3]. Barriers include difficulty accessing services, shortages of mental health professionals, stigma, and cultural beliefs [6].

In Switzerland, the prevalence of depression is 15% [7] with a 51% treatment gap [8]. Addressing these challenges requires prioritizing accessible mental health care across all income levels. Internet-based self-help interventions (IBIs) have proven effective in symptom reduction, offering scalable solutions that complement traditional therapies [9, 10]. Meta-analyses confirm their effectiveness in reducing depression, particularly in WEIRD countries, by providing flexible, location-independent support [11, 12]. Integrating these interventions could significantly expand mental health care’s reach, ensuring more equitable access to effective treatments globally [13]. However, previous studies suggest that unguided IBIs, which means having no human support at any stage, tend to be associated with higher dropout rates [14], lower uptake rates (i.e., logging into an intervention) [15, 16], lower adherence (e.g., completing modules of an intervention) [17], and sometimes also lower effects [18].

In some of the studies mentioned above, the authors propose that other forms of human interaction (such as peer-to-peer support online forums) might be beneficial for the treatment of depression [19]. In one of the meta-analyses conducted on peer support interventions for depression, evidence was found that peer support in the form of internet support groups (ISGs)/discussion groups and chat rooms led to a reduction in depressive symptoms relative to usual care [20]. It could be assumed that improvements in coping strategies, both in social interactions and regarding their health condition [21], might lead to increased supportive communication [22], which in turn could significantly enhance adherence to treatment and reduce drop-out rates [23]. However, one of the studies conducted by Andersson et al. [24] showed that there were no improvements seen in depressive symptoms due to discussion groups in the people suffering with depression. Therefore, we need more research in this direction of examining the association between IBIs using peer-to-peer support online forums as compared to the IBIs without using peer-to-peer support online forums in the treatment of depression using a randomized controlled trial to understand it better.

Furthermore, many of the studies that used IBIs for depression have been conducted on the WEIRD countries and only a few studies have been conducted in the non-WEIRD countries [25–27]. Hendriks et al.’s [28] review highlighted that most randomized controlled trials (RCTs) examining the effects of IBIs on depression originated from Western countries, with only 22% from non-Western countries, and these findings based on WEIRD populations may not generalize entirely to all cultures or ethnicities. To our knowledge, none of the studies have investigated the intercultural difference based on the usage of peer support online forums between the WEIRD and non-WEIRD population. Therefore, one of the main aims of our study is to investigate whether IBIs with peer-to-peer support online forums could improve the symptoms of depression as compared to the IBIs without peer-to-peer support and, in addition, to examine the cultural differences in the use of peer-to-peer support online forums between India and Switzerland as these countries have different cultures.

In the previous study conducted in India, traditional support structures, such as extended families and community groups, might influence how peer support is perceived and utilized [29]. Integrating these traditional structures into an online intervention could enhance its effectiveness. In contrast, in Switzerland, there is a strong emphasis on independence but also strong social support among friends [30, 31]; therefore, assessing peer support in the Swiss context and in comparison to India will extend our knowledge by understanding and addressing these cultural differences, IBIs with online peer support interventions for depression that could be tailored to meet the unique needs and preferences of participants in both India and Switzerland, potentially enhancing their effectiveness and acceptance. These cross-cultural comparisons will also contribute to guide the policymakers in creating inclusive and effective mental health policies that can be adapted across different cultures.

In this study, we will use the IBI for depression called Deprexis with peer-to-peer support and without peer-to-peer support in the French and English language through a randomized clinical trial. Deprexis is an integrative intervention that is broadly based on cognitive-behavioral therapy and has been tested in German-speaking countries [32–36], the United States [37], Brazil [38], and the German-speaking part of Switzerland [33]. This study will be the first to test its efficacy in French in Switzerland.

In addition, previous studies have evidenced that a robust reward system is linked to feelings of pleasure, emotional regulation, and overall mood stability, enhancing the ability to cope with stress and acting as a buffer against mental health issues [39–41]. Anhedonia, a core symptom of depression, involves a loss of pleasure and is often associated with dysfunction in the reward system [42, 43]. Studies using monetary rewards indicate that individuals with depression show reduced positive responses and decreased reward-seeking behavior [44], as evidenced by their performance on tasks like the Iowa Gambling Task [42]. In addition, individuals with depression frequently display deficits in social functioning and diminished motivation to engage in social interaction [45]. In one of our previous studies using the Fribourg Reward Task [46–48], reduced mood responses to monetary rewards were observed in individuals with pain symptoms in Switzerland but not in India [47, 48]. In addition, social reward might also represent a particularly salient category of reward stimuli contributing to depression [49]. Limited empirical research has been conducted to show the relationship between depression and social rewards [50]. Our study aims to further explore reward responses in individuals with depressive symptoms using the Fribourg Reward Task that includes three reward conditions (monetary, social, and no-reward) in India and Switzerland, examining intercultural differences in social and monetary rewards and testing the effects of an online treatment on these reward responses.

At the end, we also plan to conduct exploratory analyses to investigate the effects of treatment on comorbid symptoms of depression, such as stress and anxiety, which are highly comorbid with depression [50, 51]. Additionally, we will assess the impact of positive outcomes like self-efficacy, quality of life, and self-esteem on depression symptoms, as improvements in these areas have been shown to reduce depression [52–54]. We will also investigate the influence of trauma and pain on depression symptoms [55, 56]. Lastly, we aim to evaluate client satisfaction, usability, and working alliance based on technology-related measures.

### The goal of the present study

The present study, registered at ClinicalTrials.gov (NCT06480474) and Swiss National Clinical Trials (SNCTP000005917), aims to investigate (1) whether Deprexis with peer-to-peer support online forums could improve the symptoms of depression as compared to Deprexis without peer-to-peer support, (2) to examine the cultural differences in the use of peer-to-peer support online forums between a non-WEIRD country (India) and a WEIRD country (Switzerland), and (3) to examine the efficacy of Deprexis in the French-speaking part of Switzerland, and to assess the effects of the online program on mood responses to monetary and social rewards in individuals with depressive symptoms in India and Switzerland.

This study has two experimental conditions (Deprexis and Deprexis with an online forum) compared with a control condition (waiting list). The control group is used to assess the difference between having access to an intervention and having no access. We expect a superiority of Deprexis and Deprexis with the online forum group against the waiting list group (control group) and a superiority of Deprexis with the online forum group against the unguided Deprexis group. Additionally, we expect higher adherence to Deprexis with the online forum. The control group will be placed on a waiting list and will have access to the program after the initial 8 weeks.

## Methods

### Study design

This study is conducted as a randomized controlled trial. Participants will be randomly assigned to either of the three groups. The first group will use Deprexis, an internet-based self-help treatment based on cognitive-behavioral therapy, for 8 weeks. The second group will have access to Deprexis and a peer-to-peer support online forum for sharing and support. The third control group will access Deprexis after the initial 8 weeks. In total, 240 participants will be recruited, with 80 participants in each group.

### Participants

Participants will be recruited through flyers and emails, word-of-mouth, social media (e.g., Facebook, Instagram), depression-related websites, private psychotherapists, outpatient clinics in French-speaking Switzerland, and the English-speaking population from India. Interested participants will receive information on the study, and then they will be given at least 24 h to confirm their participation by signing and returning the informed consent of the study (via email). They will be screened to assess eligibility using a rapid eligibility check, using the inclusion and exclusion checklist and the Patient Health Questionnaire (PHQ-9; [57]).

The inclusion criteria are (1) providing signed informed consent; (2) being at least 18 years of age; (3) having access to a computer/laptop/tablet/smartphone with an internet connection; (4) having sufficient French language skills in Switzerland and English in India; (5) meeting criteria for mild to moderate depression as operationalized by the Patient Health Questionnaire-9 (PHQ-9 = 5–14) (PHQ-9; [57]) meeting the diagnostic criteria of the characterized depressive disorder according to the diagnostic interview by telephone; and (7) providing the emergency contact before treatment.

However, they will be excluded from the study if they present any of the following criteria: (1) having active suicidal plans (if they have a score of 2 or higher on the suicide item of the PHQ-9 [57] or with active suicidal plans in the diagnostic telephone interview; (2) having a history of psychotic disorder or bipolar disorder; and (3) changing their dosage of prescribed medication for anxiety or depression in the last month before the study. When potential participants fulfill inclusion criteria, they will be interviewed by telephone for screening using the MINI International Neuropsychiatric Interview (M.I.N.I; [58]). The current protocol is prepared in accordance with the “Standard Protocol Items: Recommendations for Interventional Trials (SPIRIT) 2013” guidelines [59].

### Description of the intervention

#### Deprexis

Deprexis is the internet-based self-help program that we will use in this study and is based on different psychotherapeutic approaches, consistent with a cognitive-behavioral perspective [32]. Deprexis has been shown to be efficacious in several previous clinical trial studies (e.g., [35, 36, 60]). Deprexis contains 10 modules that all participants can access at any time. Users of the program are encouraged to repeat all modules as many times and as often as they wish, after they have completed the full module sequence. A brief description of each module is described below:*Introduction:* Introducing the program’s function and purpose; psycho-educational overview of cognitive-behavioral therapy (CBT) model of depression (e.g., relationships among thoughts, behaviors, and feelings); exploring perceived reasons for depression; brief mindfulness exercise: learning to calmly observe the flow of thoughts and feelings; worksheet to encourage regular program use; prompting to complete mood questionnaires.*Behavioral activation:* This module includes standard behavioral activation and procedures used in different manuals, with some modifications. Users are encouraged to set activities that may satisfy basic psychological needs (e.g., social relatedness, competence, self-esteem, hedonic enjoyment).*Cognitive modification:* Similar to the first module, this one also includes standard cognitive interventions with some adaptations for the online format of the program. There is a specific focus on the mood-determining role of automatic thoughts, interactions between thoughts, emotions, etc., or techniques on acceptance.*Mindfulness and acceptance:* This module includes brief exercises to help suppress unwanted thoughts and feelings, or to learn to deal with unwelcome experiences with calmer and acceptance.*Interpersonal skills:* This module focuses on problems linked to interpersonal adjustment, it offers several suggestions to help the users to improve their interpersonal adjustment, such as tips for improved verbal and nonverbal communication, or guidelines for relationship-enhancing behaviors.*Relaxation, physical exercise and lifestyle modification:* This module includes relaxation exercises, repeated tension exercises, healthy lifestyle tips, using imagery and breathing exercises.*Problem solving: *This module includes exercises to teach a problem-solving approach linked to depression-related problems (including how to define problems in concrete terms, set achievable goals or generate solutions, etc.).*Childhood experiences and early schemas:* In this module, techniques to deal with difficult childhood memories are provided. For instance, users learn expressive writing, forgiveness, or acceptance of difficult memories.*Positive psychology interventions:* This module focuses on positive psychology based on positive experiences (e.g., happiness, well-being, life satisfaction). Exercises such as learning to enjoy positive experiences and memories, to satisfy basic needs or to cultivate strengths and talents are provided.*Dreamwork and emotion-focused interventions:* This module contains information and techniques on dream-related work and emotions. It offers techniques and exercises such as writing a dream journal, working on problem-laden dreams with positive endings or making links between dream contents and real-life problems. This module is offered for users who show positive attitudes toward such content.

The Deprexis program can be accessed from regular internet browsers, via a laptop, computer, tablet, or smartphone, through a secure website. Each participant will be provided with a password-protected account. Participants’ use of Deprexis will be automatically recorded by the program, which will allow for an automated measure of treatment compliance. Also, this program has been standardized and validated for 90 days based on evidence-based studies [32, 61]. Participants will have full access to the medical device and must first go once through all modules and are then free to repeat any module, as often as they wish. Participants are informed that they should work 30 min at least 1–2 times a week on the program. Participants can receive optional automatic reminders within the program, which also provide brief motivational-supportive messages. Moreover, participants in the experimental condition of medical devices will receive regular messages on the forum (described below) from the moderator, to encourage the use of the program and the online forum.

#### Peer-to-peer support online forum

In addition, participants in one of the experimental groups will have access to an online forum, which will be built for the study. This forum will consist of a general discussion page, in which participants will be able to ask and answer questions, and for this, the participants will be divided into a group of 10 each to share their experiences in a group if they wish to. Additionally, there will be different subforums that will each be related to specific modules of Deprexis. Participants will share their experiences and if they have any questions related to the module. A moderator will regularly check that no personal information or sensitive information is disclosed, and will once a week ask some questions on the forum to encourage participants to contribute to the forum. The moderator is not a psychotherapist and will not answer questions related to the program or advise participants on the intervention.

### Procedure

This study will be entirely online. All participants will undergo the same screening procedure, including a standardized questionnaire (PHQ-9; [57]) and a structured clinical psychiatric interview (MINI; [58]) performed via telephone. Assessments will be performed by trained research assistants from the University and supervised by a clinician from our department. Eligible participants will be randomized into one of three groups of 80 participants each: one with Deprexis only, one with Deprexis and peer-to-peer support online forum, and a control group on a waiting list, which will access Deprexis after 8 weeks.

The first group will use Deprexis, an internet-based self-help treatment based on cognitive-behavioral therapy, for 8 weeks. The second group will have access to Deprexis and a peer-to-peer support forum for sharing and support. The third control group will access Deprexis after the initial 8 weeks. Measurements will be taken at baseline (T0), mid-intervention (4 weeks, T1), post-intervention (8 weeks, T2), and follow-up (3 months after intervention, T3) (see Table 1). Participants will complete online questionnaires on RedCap (https://redcap.unifr.ch) and an adapted online version of the Fribourg reward task [46–48] at different study points (see Fig. 1).

**Table 1 Tab1:** This table demonstrates different psychometric measures used in the study

Study Periods	Screening	Baseline measures (T0)	Mid-intervention (T1)	Post-intervention (T2)	Follow-up (T3)	“End-of-study” visit
Visit	1	2	3	4	5	6
Time (weeks/day)	−2 weeks- 0	0	+ 4 weeks ± 2 weeks	+ 8 weeks ± 2 weeks	+ 20 weeks ± 2 weeks	Any time after completion or withdrawal
Patient information sheet	x					
Informed consent (after at least 24 h)	x					
PHQ-9 (including suicidal risks)	x	x	x	x	x	
MINI	x					
In-/exclusion criteria checklist	x					
SHAPS		x	x	x	x	
BIS/BAS		x	x	x	x	
MSPSS		x	x	x	x	
GAD-7		x	x	x	x	
SF-12		x	x	x	x	
RSES		x	x	x	x	
GSES		x	x	x	x	
PSS		x	x	x	x	
SSS-8		x	x	x	x	
PCL-5		x	x	x	x	
CTQ-SF		x	x	x	x	
SUS				x		
CSQ			x	x		
NEP			x	x	x	
Fribourg Reward Task		x	x	x		

*PHQ-9* Patient Health Questionnaire, *MINI* MINI International Neuropsychiatric Interview, *SHAPS* Snaith-Hamilton Pleasure Scale, *BIS/BAS* Behavioral Inhibition/Behavioral Activation System, *MSPSS* Perceived Social Support, *GAD-7* Generalized Anxiety Disorder Scale, *SF-12* Short-Form Health Survey, *RSES* Rosenberg Self-Esteem Scale, *GSES* General Self-Efficacy Scale, *PSS* Perceived Stress Scale, *SSS-8* Somatic Symptom Scale, *PCL-5* Post-Traumatic Stress Disorder Checklist for DSM-5, *CTQ-SF* Childhood Trauma Questionnaire-Short Form, *SUS* System Usability Scale, *CSQ* Client Satisfaction Questionnaire, *NEP* Negative Effects of Psychotherapy

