### Planned statistical analyses

The analysis will be done with the help of appropriate software programs (e.g., JASP or SPSS) by the end of the study. It will be conducted on the Intention-To-Treat (ITT) sample. Before analysis, all outcome variables will be tested for normality using the Kolmogorov-Smirnov test and, if necessary, transformed to obtain a normal distribution. To test for the main and interaction effects of treatment components on primary and secondary outcomes, a linear mixed-model repeated measures ANOVA with time as a within-groups factor and treatment condition as a between-groups factor will be used for the main research question. Also, repeated measures ANOVA will be used to test the effects of Deprexis on reward responses and on perceived social support in relationship to the forum utilization. We will also use mediation analyses to test our objectives. If the questionnaires have more than 30% of the missing data, they will not be used in the analysis, and for the other cases, missing data will be computed with the help of the statistics software. Interim analysis will be performed for preliminary data presentation at scientific meetings and to check data quality.

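### Table 1 lets the primary post-intervention PHQ-9 be recorded up to two weeks before the 8-week course ends; open T2 at day 56 and tie its late side to control access

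*Protocol article*

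**What the plan says.** The Abstract (Methods) sets the timetable: "The intervention lasts 8 weeks, with measurements at baseline (T0), mid-intervention (4 weeks, T1), post-intervention (8 weeks, T2"). Study design repeats the length of the course: "The first group will use Deprexis, an internet-based self-help treatment based on cognitive-behavioral therapy, for 8 weeks". The Abstract also names the endpoint: "Primary outcome: depressive symptoms at 8 weeks post-intervention". Read with the definition of T2, this is the PHQ-9 at week 8, at the end of the course.

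Table 1, under Procedure, attaches windows to the visits. T1 is allowed at "4 weeks ± 2 weeks" and T2 at "8 weeks ± 2 weeks", both counted from T0. The row "PHQ-9 (including suicidal risks") is marked at T1 and at T2.

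For the waiting list, Procedure says: "The third control group will access Deprexis after the initial 8 weeks". Planned statistical analyses uses "a linear mixed-model repeated measures ANOVA with time as a within-groups factor and treatment condition as a between-groups factor", so T1 and T2 enter as separate levels of time.

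The article states no requirement that T2 follow the end of the course, and no minimum interval between T1 and T2.

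**The concern.** The label and the window disagree. T2 is defined as a measurement after an 8-week course, but the table accepts it from week 6. A form from week 6 or 7 would enter the primary analysis as an end-of-course value although up to two weeks of treatment remain.

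If benefit is still accruing in those weeks, such forms understate the effect at week 8. Both active-versus-waiting-list contrasts would move toward zero. Forum versus Deprexis would too, if the added benefit of the forum builds over the course. A later analysis plan could say how to handle early forms, but it could not turn them into end-of-course measurements. The window is fixed in this document, so this is the place to change it.

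**Working it through.** **Inputs.** Table 1: T1 at week 4 ± 2, T2 at week 8 ± 2. Abstract and Study design: course of 8 weeks = 56 days. Procedure: control access after week 8. Days are counted from T0 with both bounds included, and the course is taken to start at T0.

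**Windows.**
- T1: (4 − 2) × 7 = 14 to (4 + 2) × 7 = 42, so days 14 to 42.
- T2: (8 − 2) × 7 = 42 to (8 + 2) × 7 = 70, so days 42 to 70.
- Course remaining when T2 opens: (56 − 42)/56 = 14/56 = 25%. On day 55 it is 1/56, about 2%.
- Part of the T2 window before day 56: 14 days of a 28-day span, or half.
- Days common to T1 and T2: day 42 only. If either bound is exclusive, there is none.
- Part of the T2 window after control access may begin: 70 − 56 = 14 days.

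**Possible dilution.** The documents give neither the time course of the effect nor the dates of forms, so this is a range under assumptions. Let the effect grow linearly to week 8 and then stay level: share at week t = min(t/8, 1).
- Week 6: 6/8 = 0.75.
- Mean over early forms spread evenly across weeks 6 to 8: (0.75 + 1)/2 = 0.875.
- All forms early: 1 − 0.875 = 12.5% of the effect lost.
- 10% of forms early: 0.10 × 0.875 + 0.90 × 1 = 0.9875, a loss of 1.25%.
- No forms early, or effect level by week 6: no loss.

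These figures cover the early side only.

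**Does moving T2 later help?** Use the same model, and let controls start Deprexis at week 8 and improve at the same rate. A control form at week t > 8 then carries (t − 8)/8 of the effect: 0.25 at week 10, and 0.125 on average over weeks 8 to 10. The active-minus-control contrast is then:
- forms in weeks 6 to 8: 0.875 − 0 = 0.875;
- forms in weeks 8 to 10: 1 − 0.125 = 0.875;
- T2 spread evenly over weeks 6 to 10: (0.875 + 0.875)/2 = 0.875;
- T2 moved to weeks 8 to 10 with control access unchanged: 0.875;
- T2 in weeks 8 to 10 with every control form recorded before exposure: 1 − 0 = 1.

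Under this model, closing the early side alone gains nothing against the waiting list. Forum versus Deprexis does not depend on control access. If its benefit builds in the same linear way, it moves from (0.875 + 1)/2 = 0.9375 to 1.

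**The case against.** **The window is only a tolerance.** The text puts T2 at 8 weeks throughout, the same ± 2 weeks applies to T1, T2 and T3, and nothing says that surveys are issued at week 6. This stands as a limit on the size, since early forms may be rare. It does not remove the conflict: the tolerance still admits forms that the definition of T2 excludes.

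**Deprexis is self-paced.** The ten modules can be opened at any time, and the advice is 30 minutes at least once or twice a week. By week 6 that is 6 to 12 sessions, and by week 8 it is 8 to 16. Some users may have been through every module before week 6, so an early date does not prove an incomplete course. This stands too, and makes dilution conditional.

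**Stronger readings that the documents do not support.**
- A reader might infer that T1 and T2 overlap broadly, or that the T1-to-T2 step loses its meaning. The windows meet on one boundary day.
- A reader might assume T2 dates spread evenly over weeks 6 to 10 with linear growth, and conclude that power falls from 80% to about 75%, at a cost of 29 participants. The documents support neither assumption. The count also takes the information loss of 1 − 0.9375² = 12.1% from the recruitment target of 240. On the 174 that the power analysis requires, it is about 21.

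**Unseen documents.** The full protocol or an analysis plan may hold rules for out-of-window forms. That is possible, but the stated window would still need correcting.

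**Conclusion.** The point holds as a conflict between Table 1 and the definition of T2. Half of the span permitted for the primary PHQ-9 falls before the course ends, with up to 25% of the course left. That needs no assumption beyond counting days from T0.

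The effect on the results is conditional and of unknown size, from nil to 12.5% of the effect at the linear-growth extreme; a modest share of early forms costs about 1%. The shared day 42 is a minor boundary matter. The change is worth making because it is cheap and most primary data are still to come: Trial status reports 9 completed T2 assessments as of August 2025, and 9/240 is 3.75% of the planned sample. It must be made together with the late side of the window, or the waiting-list contrasts may gain nothing.

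**What to change.** 1. In Table 1 and REDCap, open the T2 survey no earlier than day 56 in all three arms, with a short late tolerance.
2. End the T1 window before T2 can open.
3. Reconcile the late side of the T2 window with the statement on control access after 8 weeks, so that each control participant's T2 PHQ-9 is recorded before exposure to Deprexis.
4. Keep the T2 forms already collected. Add a sensitivity analysis of the primary contrast that excludes forms dated before day 56 and control forms dated after Deprexis access. Form date is a post-randomisation variable, so this supports the primary analysis and does not replace it.

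The cost is a table edit and a survey-opening date, with no extra visits or participants. The downside is a narrower effective window: some participants must wait to answer, with a slight risk of missed forms. That risk is greater in the control arm if the late tolerance has to be short.
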